### Phase 2: Development of a Questionnaire for Measuring Awareness of Common Skin Diseases in the Community

The literature review showed the absence of specific instruments for measuring the level of awareness in the general community of early symptoms of common skin diseases. Thus, in this second phase of the study, we aim to develop a questionnaire for measuring awareness in the general community, which will assess common skin disease knowledge, common skin disease prevention, and the intention to seek health services.

The questionnaire will be developed in 2 steps. The first step involves conducting a literature review, consultation with professional experts, and focus group discussions with persons with and without knowledge or expertise in leprosy. Questions will initially be developed in English based on expert judgement and checks by English language experts. Because the study population is Indonesian, the second step will involve translating the questionnaire into the Indonesian language.

The validity and reliability study for the developed questionnaire will be conducted in the subdistrict of Batumarmar, Pamekasan District, East Java Province, ensuring the questionnaire accurately measures the awareness of the community regarding skin diseases and produces consistent results over time and different respondents. The Batumarmar area was chosen because of its variety of geographic and community characteristics, which include rice fields, mountains, and residential areas in both urban and rural settings. Study participants will include experts in leprosy and behavioral sciences (the study supervisor), local key informants, and members of the general community.

The eligibility criteria for the validity and reliability study are as follows: (1) residents living in Batumarmar subdistrict and Pamekasan District; (2) individuals aged 18-65 years; (3) individuals willing to participate and provide informed consent; and (4) individuals able to understand and communicate in Indonesian and Madurese languages. Aside from the results of the validity and reliability test, data on demographical characteristics, such as gender, age, educational level, and occupation, will be included for analysis.

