**Methods:**

The study will be conducted in four phases: (1) development of DEDIKASI-app, (2) questionnaire development for an awareness study, (3) acceptability testing, and (4) effect measurement of DEDIKASI-app. We will adopt design thinking methodology to develop the app, involving systematic reviews, expert consultations, focus group discussions, and validation of the questionnaire on skin disease awareness. We will recruit 50 members of the community for the awareness and acceptability study and 1 health care worker per community health center to assess their perception of the app. A pilot study will assess the acceptability of DEDIKASI-app among community members and health care workers based on various constructs, with responses categorized as positive, negative, or undecided. The validity and reliability of a newly developed questionnaire on skin disease awareness will be tested, with validity results analyzed qualitatively and reliability measured using Cronbach α. The effectiveness of DEDIKASI-app in improving community awareness will be evaluated through a randomized controlled trial, using total scores, means, and SDs for control and intervention groups. Statistical significance of awareness level changes will be determined by delta change (*P* value), with *P*<.01 considered significant.

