The study population is the general community located in 21 CHCs of Pamekasan District. The participating CHCs have already been randomly allocated to either the intervention or control group using a computer-generated sequence by an independent statistician. The intervention group comprises Tlanakan, Bandaran, Pademawu, Sopaah, Galis, Larangan Bedung Kadur, Batumarmar, Teja, and Kowel, and the control group comprises Larangan, Talang, Proppo, Panaguan, Palengaan, Pakong, Waru, Tampojung Pregi, Pasean, Pengantenan, and Bulangan Haji. Allocation concealment was ensured by using sequentially numbered, sealed, opaque envelopes, opened only after enrolment of each cluster. Research assistants will enroll participants through door-to-door recruitment*.* To reduce information contamination, we will ensure geographical separation of intervention and control CHCs where feasible. Pamekasan District, located on Madura Island in East Java Province, covers an area of approximately 792 square kilometers, with a population density of around 850 people per square kilometer. The district is divided into 13 subdistricts, with substantial distances between them; for example, the distance between Batumarmar (a northern subdistrict) and Proppo (a central subdistrict) is approximately 25 kilometers, often requiring over an hour’s travel due to rural road conditions. Given this geographic spread and limited daily intervillage interactions, the risk of information spillover between intervention and control clusters is considered minimal. Baseline and postintervention surveys will be conducted within a short period of a fixed 4-week window across all clusters to minimize variation due to external influences such as health campaigns or seasonal trends. Data collectors will follow the arranged schedule based on the study procedure. For eligibility to participate in the study, participants must be a resident of Pamekasan District, especially in the working area of the 21 CHCs; aged 18-65 years; willing to participate in the study and provide informed consent; and an android or smartphone user. The final criterion might not apply to the control group.

Data regarding the effectiveness of DEDIKASI-app as a strategy to increase awareness and early detection of leprosy and other common skin diseases will be collected using the validated questionnaire that will be developed in phase 2.

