### Statistical Analysis

Results of validity and reliability testing of the community awareness questionnaire developed in phase 2 will be analyzed using both descriptive and analytical statistics. Demographic data will be analyzed descriptively, while the validation and reliability of the questionnaire will be assessed statistically using Pearson correlation and Cronbach α, respectively. Content and face validity will be qualitatively used to avoid question item ambiguity, ensure clarity and relevancy, and ensure that the questions are not judgmental, intrusive, or distressing to target participants [34]. The questionnaire will be administered through an interview setting, with all selected respondents interviewed at 2 points: a preintervention interview and a postintervention interview conducted approximately 4 weeks later (during the intervention study in phase 4).

During the third phase, the questionnaire developed in phase 2 will be used to collect the data on awareness in the general community. All responses to the questions will be given numerical scores based on correct or positive answers. The total score will be calculated, while the mean range will be used to illustrate the distribution and variation of scores. To measure the impact of the intervention, the change in scores (delta change) between preintervention and postintervention assessments will be calculated for each group. The Wilcoxon signed-rank test will be used to compare paired preintervention and postintervention scores within each group. A *P* value of <.01 will be considered statistically significant, indicating improvements in respondents’ knowledge, prevention practices, and health-seeking behavior.

The acceptability test for DEDIKASI-app will be conducted during the third phase, using a survey based on the TAM. A Likert scale will be used as a scoring system. The results from both community members and HCWs will be descriptively analyzed and presented using a frequency table.

Data from the randomized controlled trial in the fourth phase will be analyzed using SPSS version 21 (IBM Corporation). We will conduct a descriptive analysis by calculating the either the mean or median values of the awareness scores and the count of reported common skin disease cases through DEDIKASI-app. The choice between mean or median will depend on the distribution of the scores. We will also use a box plot diagram to visually compare the measurements between the 2 groups.

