For assessing the effectiveness of DEDIKASI-app as an intervention for enhancing awareness compared to the control group, we will apply an independent sample *t* test if the data exhibit a normal distribution. If the data distribution is not normal, we will use the Mann-Whitney test. All statistical analyses will be performed at a significance level of .05, with a 95% CI (or using the IQR if medians are used).

Missing data will be described and explored. We acknowledge that incomplete case analysis can introduce bias and will consider appropriate imputation techniques during final analysis depending on the extent and pattern of missingness. We will include the outcomes of all participants (intention-to-treat), regardless of the extent the intervention group used DEDIKASI-app.

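### The new questionnaire is said to give consistent results over time, but the only reliability statistic named, Cronbach α, comes from a single interview

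*Protocol article*

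**What the plan says.** The Phase 2 section of the Methods gives the purpose of the validity and reliability study in Batumarmar. It is to ensure that the questionnaire measures awareness accurately and "produces consistent results over time and different respondents".

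The statistics are named in Statistical Analysis: "the validation and reliability of the questionnaire will be assessed statistically using Pearson correlation and Cronbach α, respectively". The Abstract describes the same work "with validity results analyzed qualitatively and reliability measured using Cronbach α". The two places differ on how validity is assessed, but both leave Cronbach α as the only reliability measure.

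The only interviews at two time points are "a preintervention interview and a postintervention interview conducted approximately 4 weeks later (during the intervention study in phase 4".

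Phase 4 outcome data are "collected using the validated questionnaire that will be developed in phase 2". For these, "the change in scores (delta change) between preintervention and postintervention assessments will be calculated for each group", and "The Wilcoxon signed-rank test will be used to compare paired preintervention and postintervention scores within each group". A P value below .01 is then taken to show gains in knowledge, prevention and care seeking. The arms are compared with an independent-samples t test, or a Mann-Whitney test if scores are not normal.

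**The concern.** The document claims a property and names the statistic meant to support it, and that statistic cannot show the property. Cronbach α describes how far the items agree with one another at one sitting. It carries no information on whether the same person would score the same four weeks later.

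Two things are at stake. The first is the standing of the instrument. Developing it is aim 2, and Phase 2 reports that no specific instrument existed, so the document offers no earlier retest evidence. The second is the within-group analysis. If people score higher at the second interview simply because they have met the questions before, the signed-rank test will show a rise, and the stated interpretation will call it improvement.

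**Working it through.** The plan gives no figure for reliability, so there is none to reproduce. The check is mainly a comparison of passages, with two short calculations.

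**1. Could the Pearson correlation be the retest coefficient?** No. In the Statistical Analysis sentence, the closing word assigns Pearson to validation and Cronbach α to reliability. The sentence does not say what Pearson is computed between, but it is not presented as reliability over time.

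**2. Is there a phase 2 retest?** None is described. The pre and post interviews belong to phase 4, and one arm receives the intervention between them.

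**3. Could a high α imply stability?** Assume a 20-item scale. Each item is 0.6 × factor + 0.8 × independent error, and a share *s* of the factor variance carries over to a second occasion. These values are assumptions; the document gives no item count.

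- Variance of the total: 20² × 0.36 + 20 × 0.64 = 144 + 12.8 = 156.8.
- α = (20/19) × (1 − 20/156.8) = 0.918, whatever the value of *s*.
- Item-total correlation = (20 × 0.36 + 0.64)/√156.8 = 7.84/12.52 = 0.626, whatever the value of *s*.
- Retest correlation = *s* × 144/156.8 = 0.918 × *s*.

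| *s* | α | Item-total r | Retest r |
|---|---|---|---|
| 0.3 | 0.918 | 0.626 | 0.28 |
| 0.5 | 0.918 | 0.626 | 0.46 |
| 0.7 | 0.918 | 0.626 | 0.64 |
| 0.9 | 0.918 | 0.626 | 0.83 |

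A simulation of the same model (20,000 respondents) gave α of 0.918 to 0.919 and retest correlations of 0.27, 0.45, 0.65 and 0.83. So the single-occasion statistics do not move while stability changes threefold.

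**4. How large a re-interview shift would the within-group test flag?** This is an illustration only. Take SD 5 from the sample-size paragraph as the SD of one score, 300 pairs in an arm (half of the expected 600), an assumed pre-post correlation r, and a normal approximation to the paired test. The SD of change is 5√(2(1 − r)), and the mean shift that reaches P = .01 is 2.576 × SD of change/√300.

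- r = 0.3: 2.576 × 5.92/17.32 = 0.88 points.
- r = 0.5: 2.576 × 5.00/17.32 = 0.74 points.
- r = 0.7: 2.576 × 3.87/17.32 = 0.58 points.

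Under these assumptions, an observed shift of less than one point from any cause meets the criterion. The article does not give the score range, so how likely such a shift is cannot be judged from it.

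**5. What happens in the between-arm comparison?** Both arms are interviewed at the same two points. A re-interview shift common to both cancels in the difference. Random instability adds noise to it without bias.

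**The case against.** The phrase in Phase 2 can be read as a general statement of what a reliability study is for, since it promises no retest interval or coefficient. A journal article may also leave such detail to a full protocol. The first part has some force, and for that reason the finding is that this document plans no test, not that stability was never examined. The second part is weaker: the article does name its reliability statistic, twice, and what it names does not match the claim.

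The stronger defence is that effectiveness is judged against a randomised control group, which deals with shared re-interview effects. This stands. A reader might infer that the main trial result is unreliable, and the documents do not support that.

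A reader might also infer a loss of power, because the SD of change exceeds 5 when the pre-post correlation is below 0.5. The documents do not support this either. They give no correlation and call 5 only a population SD. They do not say whether the between-arm test uses change or post scores, and the sample-size calculation is still outstanding. Health centres are allocated as whole clusters, which such a calculation would ignore. Reporting a stability coefficient would in any case alter neither the power nor the P value.

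Finally, the article calls the questionnaire validated, and in Strengths and Limitations relies on that as mitigation for expectation bias. It nowhere claims that the instrument is reliable for measuring change, so that charge should not be made.

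**Conclusion.** The point holds in a limited form. The document claims stability over time, names only a single-occasion reliability statistic, and describes no phase 2 retest. This rests on the text alone and needs no assumption.

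The consequence is confined to two places: the reliability claim for the new instrument under aim 2, and the reading of the within-group signed-rank results as improvement. For the second, the risk is a systematic shift at re-interview, since random instability alone would not push scores one way. The randomised contrast between arms is not biased by the omission. The 0.28 to 0.83 range depends on the assumed scale and shows only that α cannot reveal instability. The shifts of 0.58 to 0.88 points are illustrative, and the verdict does not depend on them.

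The point is worth correcting before publication, because it changes what may be said about the questionnaire.

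**What to change.** In Methods, Phase 2, limit the reliability claim to internal consistency.

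In Methods, Statistical Analysis, add wording such as:

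> Stability over about 4 weeks will be estimated from the control-arm pre and post interviews as an absolute-agreement intraclass correlation, with a 95% CI that allows for clustering by CHC, together with the standard error of measurement. Within-group change in the intervention arm will be interpreted only against the shift in the control arm.

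The absolute-agreement form matters because it counts a uniform rise between interviews as disagreement. A consistency form would hide it.

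**Cost.** A few lines of analysis and no new data. The article reports that phase 2 is complete and that trial data collection has ended, so a phase 2 retest can no longer be planned ahead, but the control-arm interviews already exist. With 11 control centres listed, the clustered interval will be approximate.

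**Downside.** The control-arm coefficient mixes instability, true change, learning and recall of earlier answers. Recall can raise it, and true change or learning can lower it. It is therefore an indirect estimate that may be biased in either direction, and should be reported as such.

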### Phase 3: Awareness Study and Acceptability Test of DEDIKASI-App

#### Awareness Study

Implementation of the awareness study in the general community will follow a cross-sectional mixed-method approach. The population being studied is the general community in Pamekasan District. Fifty respondents will be recruited from 4 CHCs that were randomly selected based on their representativeness of urban and rural areas in Pamekasan District. Two CHCs were chosen to represent urban areas (Teja and Proppo), while the other 2 represent rural areas (Sopa’ah and Galis). Recruitment of respondents will be conducted using a simple random sampling technique. The number of respondents is based on a minimum sample size proposed by Terwee et al [30] for the measurement properties of health status questionnaires.

The eligibility criteria for respondents are as follows: (1) residents living in the 4 CHCs in Pamekasan District, (2) individuals aged 18-65 years, (3) individuals willing to participate and provide informed consent, and (4) individuals able to understand and communicate in Indonesian and Madurese languages.

#### Acceptability Test

In parallel with the awareness study, acceptability testing for DEDIKASI-app will be conducted with the same 50 respondents selected for the awareness study. This study aims to measure the acceptability level of the community toward DEDIKASI-app and to assess their perception toward its use. In addition, 21 HCWs (1 from each of the 21 CHCs) will be included in an acceptability test of the DEDIKASI-HCW app to assess their perception of its use. We will include HCWs who actively coordinate with leprosy supervisors at the district health office level.

DEDIKASI-app will be shown to all participants. Community and HCWs’ acceptability, defined as the degree to which users are willing to adopt and use a new technology influenced by key psychological and behavioral factors, will be conducted using a survey based on the technology acceptance model (TAM). The TAM is widely adopted to assess the acceptability of health technologies within the 4 constructs of perceived usefulness, perceived ease of use, attitude, and behavioral intention to use [31,32]. Based on previous studies [28,29], the following 4 constructs will be added: security and privacy, technology literacy, quality of information, and benefit. For the TAM questionnaire with these added constructs, we will not conduct a separate validation, as the reasons for including these constructs have already been established and validated in prior studies. However, in the current study, we will train the research assistants to carefully observe whether the respondents understand the questions during administration to ensure clarity and comprehension. A 5-point Likert scale will be used to quantify the responses.

### Phase 4: Randomized Controlled Trial of the Effectiveness of DEDIKASI-App to Increase Early Detection of Skin Diseases Including Leprosy

The fourth phase is an randomized controlled trial aimed to assess the effectiveness of DEDIKASI-app as a strategy to increase awareness and early detection of leprosy and other common skin diseases.

The sample size will be calculated using the following formula for hypothesis testing for 2 population means (2-sided test) [33]:

The following values will be used: level of significance (α)=5%; power of the test (1-β)=90%; population SD (σ)=5; and population variance (σ^2^)=25. The population mean (µ_1_) will be obtained after the awareness study in the second phase; as there was no previous study available, µ_2_ represents the anticipated population mean of the intervention group. Sample size will be calculated afterward; however, we will expect to obtain 600 participants.

The study population is the general community located in 21 CHCs of Pamekasan District. The participating CHCs have already been randomly allocated to either the intervention or control group using a computer-generated sequence by an independent statistician. The intervention group comprises Tlanakan, Bandaran, Pademawu, Sopaah, Galis, Larangan Bedung Kadur, Batumarmar, Teja, and Kowel, and the control group comprises Larangan, Talang, Proppo, Panaguan, Palengaan, Pakong, Waru, Tampojung Pregi, Pasean, Pengantenan, and Bulangan Haji. Allocation concealment was ensured by using sequentially numbered, sealed, opaque envelopes, opened only after enrolment of each cluster. Research assistants will enroll participants through door-to-door recruitment*.* To reduce information contamination, we will ensure geographical separation of intervention and control CHCs where feasible. Pamekasan District, located on Madura Island in East Java Province, covers an area of approximately 792 square kilometers, with a population density of around 850 people per square kilometer. The district is divided into 13 subdistricts, with substantial distances between them; for example, the distance between Batumarmar (a northern subdistrict) and Proppo (a central subdistrict) is approximately 25 kilometers, often requiring over an hour’s travel due to rural road conditions. Given this geographic spread and limited daily intervillage interactions, the risk of information spillover between intervention and control clusters is considered minimal. Baseline and postintervention surveys will be conducted within a short period of a fixed 4-week window across all clusters to minimize variation due to external influences such as health campaigns or seasonal trends. Data collectors will follow the arranged schedule based on the study procedure. For eligibility to participate in the study, participants must be a resident of Pamekasan District, especially in the working area of the 21 CHCs; aged 18-65 years; willing to participate in the study and provide informed consent; and an android or smartphone user. The final criterion might not apply to the control group.

Data regarding the effectiveness of DEDIKASI-app as a strategy to increase awareness and early detection of leprosy and other common skin diseases will be collected using the validated questionnaire that will be developed in phase 2.

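### The planned sample-size formula makes no allowance for randomising 21 whole CHCs, so its 90% power is overstated at any positive ICC, and 90% power is not shown for the expected 600

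*Protocol article*

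**What the plan says.** The section on phase 4 in the protocol article fixes the method of sizing: "The sample size will be calculated using the following formula for hypothesis testing for 2 population means (2-sided test". Its numerical inputs are "level of significance (α)=5%; power of the test (1-β)=90%; population SD (σ)=5", with the variance given as 25. Neither mean has a value. On the first, "The population mean (µ_1_) will be obtained after the awareness study in the second phase"; on the second, "µ_2_ represents the anticipated population mean of the intervention group". The size is to be worked out later, and 600 participants are expected.

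The next paragraph of the same section sets the unit of randomisation: "The participating CHCs have already been randomly allocated to either the intervention or control group". There are 21 CHCs, and the text itself calls them clusters.

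No ICC, design effect, cluster size or number of clusters is listed among the inputs. The Statistical Analysis section, which plans an independent-samples t test or a Mann-Whitney test between groups, supplies none either.

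**The concern.** The listed inputs are those for individually randomised, independent people. Here about 600/21 = 28.6 residents share each allocation. If residents of one CHC resemble each other in awareness, each adds less information than an independent person would, and the variance of the difference between arms is larger than the formula assumes.

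This is a planning matter, separate from the choice of test. Even if the analysis handles clustering correctly, the 90% used for sizing would not be the power of the trial.

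What is at stake is how the result is read. Results, Current Progress says that data collection has ended and analysis is under way, so the number enrolled can no longer be changed. If a null result is reported against a planned 90% power, it may be taken as evidence that the app does not work when the trial could have missed a difference of the planned size.

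**Working it through.** **Inputs from the article:** "level of significance (α)=5"% two-sided; "power of the test (1-β)=90"%; "population SD (σ)=5; and population variance (σ^2^)=25"; 600 expected; 21 CHCs.

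**Assumptions, not in the article:** ICC of 0.01 to 0.10; equal cluster sizes; 10 and 11 CHCs per arm, to match the stated 21; SD 5 applies to the outcome analysed. The formula itself is not legible in the text available, so its form is taken from its description and listed inputs.

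**Step 1. Can 600 be reproduced?** No, because the difference in means has no value. Solving backwards for the difference at which 300 per arm gives 90% power:

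(1.960 + 1.282) × 5 × √(2/300) = 1.32 points, or 1.32/5 = 0.26 SD.

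**Step 2. What the formula returns.** n per arm = 2 × 25 × (1.960 + 1.282)² / difference². The total N is 1052 for 1 point, 468 for 1.5, 264 for 2 and 118 for 3.

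**Step 3. Power of those numbers in 21 clusters.** With m = N/21, the design effect is 1 + (m − 1) × ICC and the standard error is 5 × √(4/N × design effect). Power comes from the noncentral t on 21 − 2 = 19 df.

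| Target difference | N from formula | ICC 0 | ICC 0.01 | ICC 0.05 | ICC 0.10 |
|---|---|---|---|---|---|
| 1 | 1052 | 87% | 71% | 38% | 24% |
| 1.5 | 468 | 87% | 80% | 57% | 41% |
| 2 | 264 | 87% | 83% | 69% | 56% |
| 3 | 118 | 87% | 86% | 80% | 72% |

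The ICC 0 column shows that about 3 points of the shortfall come from using 19 df in place of the normal distribution. The rest is the design effect.

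**Step 4. Power of 600 in 21 clusters.** Here m = 28.57. Worked at ICC 0.05: design effect 1 + 27.57 × 0.05 = 2.38; effective N 600/2.38 = 252; standard error 5 × √(2/300 × 2.38) = 0.63; noncentrality at 1.32 points 1.32/0.63 = 2.10, against a critical t of 2.093; power 51%.

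| ICC | Design effect | Effective N | Power at 1.32 | Power at 2 | Power at 2.5 | Power at 3 | Detectable at 90% |
|---|---|---|---|---|---|---|---|
| 0.01 | 1.28 | 470 | 78% | 98% | >99% | >99% | 1.58 |
| 0.02 | 1.55 | 387 | 69% | 96% | >99% | >99% | 1.74 |
| 0.05 | 2.38 | 252 | 51% | 85% | 96% | >99% | 2.15 |
| 0.10 | 3.76 | 160 | 35% | 67% | 85% | 95% | 2.71 |

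Under a normal reference the powers at 1.32 points are 82%, 74%, 56% and 39%, so the pattern does not depend on the choice of reference distribution.

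**The case against.** The strongest reply is that the article never claims 90% power for 600. The 90% is an input to a calculation still to be done, and 600 is an expected enrolment. The 1.32 points is this review's back-solution, and no such difference is named in the article. If 600 is a round figure set well above what the formula would return, power can survive clustering: at 2.5 points it is 96% at ICC 0.05, and at 3 points about 95% or more throughout the range.

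That stands. A reader might infer from the missing cluster term that 600 participants are too few, or that the trial had only an even chance of detecting its planned effect. The article supports neither. It gives no planned effect and no ICC, and the 51% needs both 1.32 points and an ICC of 0.05.

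The reply does not rescue the calculation. It remains an individual-level formula applied to a cluster-randomised design, and the shortfall in step 3 appears at every target difference tried. Nor is this a detail that an article may leave to a fuller document, since the method and its inputs are stated here.

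It is also fair to say that the unadjusted between-group test bears more directly on the validity of the inference. That is a separate point.

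**Conclusion.** The concern holds in a limited form. The planned calculation ignores the randomisation of 21 CHCs, so the N it returns for any target difference has less than the stated 90% power at any positive ICC: from 86% down to 24% over the differences and ICCs tabulated. For the expected 600, 90% power is not shown, which is different from being shown to be absent. Power there depends on two unstated quantities. It is 78% to 35% if the difference of interest is 1.32 points, 98% to 67% at 2 points, and about 95% or more at 3 points, across ICCs of 0.01 to 0.10.

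The absence of a cluster term among the listed inputs is read directly from the article. The sizes rest on the assumed ICC range, SD 5 and equal clusters; unequal clusters would raise the design effect.

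**What to change.** Keep enrolment as it is. In the phase 4 sample-size paragraph:

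- Replace the individual-level calculation with one that multiplies the variance by 1 + (m − 1) × ICC, with m about 29, 21 clusters and a t reference on 19 df.
- State the target difference used and how it relates to 600.
- Estimate the ICC from the trial's own baseline scores by CHC, pooled over arms. Show a range around it, because 21 CHCs will estimate it imprecisely.
- Replace the 90% power statement with the difference detectable at 90% power: about 1.58, 1.74, 2.15 and 2.71 points at ICC 0.01, 0.02, 0.05 and 0.10. Read a null result against that figure.

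Because data collection is complete, this is a statement of what the trial could detect and does not alter the design. The cost is one recalculation and revised wording, with no added participants. The downside is that the stated power or detectable difference becomes less favourable.

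### The 90% power rests on a formula for independent individuals with no stated difference, so it is not substantiated for a trial that randomises 21 health centres

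*Protocol article*

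**What the plan says.** In the Phase 4 section the method is a "formula for hypothesis testing for 2 population means (2-sided test"). The values listed are "level of significance (α)=5"%, "power of the test (1-β)=90"% and "population SD (σ)=5; and population variance (σ^2^)=25". For the means, "The population mean (µ_1_) will be obtained after the awareness study in the second phase", while µ2 is described only as the anticipated mean under intervention, without a number. The paragraph closes: "Sample size will be calculated afterward; however, we will expect to obtain 600 participants".

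The next paragraph of the same section reads "The study population is the general community located in 21 CHCs of Pamekasan District". It says that the CHCs themselves were allocated by a computer-generated sequence, with envelopes opened after each cluster was enrolled. The Statistical Analysis section plans an independent-sample t test for the between-group comparison, or a Mann-Whitney test if the data are not normal. Both are described at the level of the individual participant. The abstract and Current Progress say that trial data collection has finished and analysis is under way.

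**The concern.** A two-means formula treats every participant as independent. Here the allocation unit is the CHC, and people served by one CHC are likely to resemble each other in awareness scores. The variance of the difference then grows by 1 + (m − 1) × ICC, where m is the number of participants per CHC, so the formula's N is too small for the power it was solved for. The formula also cannot be completed from what is given: N depends on µ1 − µ2, and learning µ1 alone does not supply that difference. The expected 600 therefore has no stated link to the 90%.

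At stake is what readers can infer from the 5% and 90% pair. For this design neither is secured: the power because the calculation ignores clusters, and the 5% because the planned test ignores them too.

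**Working it through.** **Inputs from the protocol article.** Two-sided α = 0.05, power 90%, SD 5, expected total 600, 21 CHCs. Hence m = 600/21 = 28.6.

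**Assumptions.** ICC of .01, .05 and .10 (the article gives none); equal cluster sizes; 10 versus 11 CHCs. The printed intervention list can be read as 9 or 10 names, depending on a possibly missing comma. With 9 versus 11, power changes by less than 2 percentage points.

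**Step 1: can 600 be reproduced?** Not forwards, because no difference is given. The unadjusted formula, n per arm = 2 × 5² × (1.960 + 1.282)² / d², gives these totals:

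| Difference d (points) | Total N, clustering ignored |
|---|---|
| 1.0 | 1052 |
| 1.32 | 604 |
| 1.33 | 596 |
| 1.5 | 468 |
| 2.0 | 264 |
| 3.0 | 118 |

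Solving backwards for 300 per arm: d = (1.960 + 1.282) × 5 × √(2/300) = 1.32 points, or 0.26 SD. The article does not state this value; it is only the difference at which 600 and 90% agree under the named formula.

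**Step 2: allow for clusters.** Design effect DE = 1 + 27.6 × ICC. The standard error of a cluster-level comparison is 5 × √[DE/28.6 × (1/10 + 1/11)] = 0.409 × √DE. Power comes from the noncentral t distribution with 10 + 11 − 2 = 19 df. The difference detectable with 90% power is 3.42 standard errors.

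| Assumed ICC | DE | Effective N | SE | Power at 1.32 | Power at 2 | Power at 3 | Detectable difference at 90% |
|---|---|---|---|---|---|---|---|
| .01 | 1.28 | 470 | 0.46 | 78% | 98% | >99% | 1.58 |
| .05 | 2.38 | 252 | 0.63 | 51% | 85% | >99% | 2.15 |
| .10 | 3.76 | 160 | 0.79 | 35% | 67% | 95% | 2.71 |

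A small part of the loss comes from having only 19 df: at ICC 0 the same test has 87% power at 1.32 points. With the design effect alone and a normal approximation, the figures at 1.32 points are 82%, 56% and 39%.

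**Step 3: would more participants help?** With 10.5 CHCs per arm on average, the required cluster size under the normal approximation is m = 300 × (1 − ICC) / (10.5 − 300 × ICC). At ICC .01 this gives a total of about 832. At ICC .05 the denominator is 10.5 − 15 = −4.5, so no number of participants in 21 CHCs reaches 90% for 1.32 points.

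**Step 4: the test actually planned.** An individual-level test that ignores clusters uses a standard error too small by √DE. Its true type I error is about 2 × [1 − Φ(1.96/√DE)]:

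- ICC .01: 1.96/1.13 = 1.74, giving 8%
- ICC .05: 1.96/1.54 = 1.27, giving 20%
- ICC .10: 1.96/1.94 = 1.01, giving 31%

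**The case against.** The strongest reply is that no stated figure is computed wrongly. A reader might infer that 600 was derived from the formula; the article says the opposite, since the calculation is still to come and 600 is only expected. A reader might also infer that 600 is too few. That is not supported either: power is undefined without a difference, and the 1.32 points is back-solved. For a 2-point difference the cluster-level test with 600 keeps 90% power up to an ICC of about .038, and for 2.5 points up to about .080. Both replies stand, and they limit the point to power that is not substantiated.

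A third tempting reading is that the main harm is a null result misread as evidence against the app. The power losses in the table belong to a cluster-level test, which the article does not plan. Under the planned unadjusted test, the main danger is a false positive. This also stands.

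Other replies carry less weight. The article explains that no earlier study was available, which excuses an unknown µ1 but not the absence of a target difference. The formula itself is missing from the text available for review, so the absence of a design effect rests on the named method and its listed inputs; neither has any place for clusters. Finally, a condensed article may leave detail to a full protocol or analysis plan, but this one does specify the calculation and its inputs, and they do not fit the allocation unit described in the next paragraph.

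**Conclusion.** The point holds in a limited form. The named calculation is for independent individuals, the trial randomises 21 CHCs, and no difference is stated, so 90% power is not substantiated. Any N taken from that formula gives less than 90% power for its own target difference whenever the ICC is above zero. The documents do not show that 600 is inadequate, because that depends on two unstated quantities.

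The size is illustrative: at SD 5 and assumed ICCs of .01 to .10, the detectable difference at 90% power moves from 1.32 points, ignoring clusters, to about 1.6 to 2.7 points. These figures assume equal cluster sizes and an SD of 5 for the score analysed. If the comparison is made on pre-to-post change, which the article also mentions, the SD and ICC may differ and the figures with them.

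**What to change.** Keep the 600 participants and the 21 CHCs; data collection has finished, so recruitment cannot change. Rewrite the sample-size paragraph in place of the unqualified 90%:

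- State the target difference in awareness score, justified by what change matters on the questionnaire and not by the trial's results.
- Give the difference detectable with 90% power over a stated ICC range, using the number of CHCs per arm and 19 df (18 if the arms are 9 and 11). At SD 5 this is about 1.6, 2.2 and 2.7 points for ICC .01, .05 and .10.
- Repeat it with the SD seen in the 50-person awareness survey as a sensitivity value.

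The restated figure must describe the test that is used. So replace the unadjusted t test or Mann-Whitney test in Statistical Analysis with a cluster-adjusted between-group comparison: a mixed model with CHC as a random effect, or a t test on CHC means. Restating the power without this change would leave the type I error problem in place.

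The cost is one rewritten paragraph and one changed analysis sentence, with no new participants. The drawback is that the stated figure becomes less favourable. As analysis is under way, the change should be made and dated before between-group results are examined, or declared as made later.
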